### Sample size

The total sample size is 350 patients, with 175 participants assigned randomly to each arm. This will include a dropout rate of 1%. This sample size is based on VISION-UK data which showed that morbidity associated with troponin elevation (≥15 ng L^−1^) in the first 24 h after surgery is experienced by 59% of patients with similar characteristics.^32^ In contrast, 41% of patients without any troponin elevation sustained postoperative morbidity, representing a 31% lower relative risk of morbidity after surgery compared with patients who sustained myocardial injury defined by elevation in troponin. Assuming a conservative relative risk reduction of 25%, 173 patients will be required in each arm if ivabradine reduces the incidence of myocardial injury-associated morbidity from 59% (placebo) to 44% (α=0.05; 1–β=0.8).

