**Clinical trial registration:**

ISRCTN12903789.

At least 300 million surgical operations are estimated to occur each year globally.^1^ Myocardial injury after noncardiac surgery occurs in ∼40% of the highest risk older patients with comorbidity who undergo elective major surgery.^2^ Myocardial injury is defined by prognostically significant elevations in troponin I or T using high-sensitivity troponin assays.^3^ Although the majority of these episodes that occur within 48 h of surgery are asymptomatic, myocardial injury after noncardiac surgery is independently and strongly associated with both short-term morbidity^4^^,^^5^ and longer-term complications including mortality.^6^^,^^7^

Because myocardial injury usually occurs in the absence of chest pain and electro- and/or echocardiographic changes consistent with myocardial infarction,^8^ numerous non-thrombotic mechanisms have been postulated to trigger this sentinel pathophysiological event.^9^ Supply–demand mismatch may occur as a result of haemodynamic lability^10^^,^^11^ and tachycardia,^12^^,^^13^ which increase myocardial oxygen consumption. Higher preoperative heart rates >83 beats min^−1^ are independently associated with myocardial injury.^12^^,^^13^ However, limiting potentially injurious tachycardia with beta-blockers and clonidine resulted in hypotension and ischaemic stroke.^14^ Poise-1 highlighted the hazards of using fixed dose, extended-release beta-blockers without titration or individualised dosing.^15^

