### Trial outcomes

#### Primary endpoint

The primary endpoint is a composite of myocardial injury associated with morbidity within 7 days of surgery. Myocardial injury is defined using the VISION study criteria,^3^ provided high-sensitivity troponin T (Elecsys; Roche Diagnostics; Rotkreuz, Switzerland) concentration ≥15 ng L^−1^ on day 1, 2, or 3 after surgery or increase of ≥5 ng L^−1^ from the preoperative value on day 1, 2, or 3 after surgery when the preoperative value is ≥15 ng L^−1^. The Elecsys Troponin T hs assay uses two monoclonal antibodies specifically directed against human cTnT, recognising two epitopes (amino acid positions 125–131, 136–147) located in the central part of the CTnT protein comprising 288 amino acids. Postoperative morbidity is systematically recorded using the Postoperative Morbidity Survey (POMS) on day 3 and day 7 after surgery.^30^

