### Statistical analysis

A full statistical analysis plan will be developed before any interim or final analysis and published online at https://www.qmul.ac.uk/ccpmg/sops--saps/statistical-analysis-plans-saps/. During the recruitment period, the trial statistician will perform a safety analysis if specifically requested by the DMEC, as outlined in the DMEC charter.

All analyses will be conducted according to the intention-to-treat principle, with all randomised participants with a recorded outcome analysed according to the treatment to which they were randomised. The primary outcome will be analysed using a logistic regression model. The model will be adjusted for minimisation variables (trial centre and planned surgical procedure [surgery involving the gut, all other surgery]). The model will also be adjusted for pre-specified baseline covariates entered into the model as fixed factors. Preoperative heart rate before the first IMP administration will be included as a continuous variable, assuming a linear association with the outcome. The magnitude of the treatment effect will be reported as an adjusted odds ratio (OR) with a 95% confidence interval (CI). Significance will be set at *P*<0.05. Similar analyses of secondary outcomes will be undertaken by intention-to-treat principle, according to the treatment to which they were randomised.

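### The 59% placebo rate in the sample size is a morbidity rate among troponin-positive patients, not the rate of the joint primary endpoint in all randomised patients, so the stated 80% power is not supported

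*Protocol article*

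**What the plan says.** All references are to the protocol article.

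- **Primary endpoint:** "The primary endpoint is a composite of myocardial injury associated with morbidity within 7 days of surgery". Injury is defined by high-sensitivity troponin T on day 1, 2 or 3, and morbidity by the Postoperative Morbidity Survey (POMS) on days 3 and 7.
- **Statistical analysis:** the intention-to-treat set is "all randomised participants with a recorded outcome analysed according to the treatment to which they were randomised". Nothing limits it to patients with raised troponin, and the inclusion criteria do not require a raised troponin.
- **Sample size, source:** morbidity associated with troponin elevation "in the first 24 h after surgery is experienced by 59% of patients with similar characteristics". The next sentence says that "41% of patients without any troponin elevation sustained postoperative morbidity" and describes this as a 31% lower relative risk than in patients with myocardial injury.
- **Sample size, calculation:** "173 patients will be required in each arm if ivabradine reduces the incidence of myocardial injury-associated morbidity from 59% (placebo) to 44" per cent, at α = 0.05 and 80% power. With 1% dropout this becomes 175 per arm, 350 in total.
- **Introduction:** "Myocardial injury after noncardiac surgery occurs in ∼40% of the highest risk older patients" with comorbidity having elective major surgery.
- **Discussion:** an earlier cohort, cited to the same reference as the 59%, had 992 patients with elevated troponin within 12 h of surgery and 3343 without.

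**The concern.** The calculation treats 59% as the share of all placebo patients who will have the primary endpoint. The source sentences give something else: the share with morbidity among those whose troponin rose. A patient who never has myocardial injury cannot have injury with morbidity, yet still counts in the denominator. Using the conditional rate as the rate in all patients amounts to assuming that every placebo patient has injury.

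This matters because the article claims 80% power, sets significance at P<0.05, and says in its closing summary that the study will establish whether heart rate control reduces morbidity. If the true endpoint rate is well below 59%, the trial has far less chance of detecting the assumed 25% reduction, and a non-significant result would carry much less information than the stated power implies.

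**Working it through.** **Step 1. Reproduce the stated figure.** Two-sided α = 0.05, power 0.80, pooled two-proportion formula without continuity correction:

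n per arm = [1.960 × √(2p̄(1−p̄)) + 0.842 × √(p₁(1−p₁) + p₂(1−p₂))]² / (p₁−p₂)²

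With p₁ = 0.59, p₂ = 0.44 and p̄ = 0.515: (1.385 + 0.588)² / 0.15² = 173.1. Power at 173 per arm is 80.0%, and 173/0.99 rounds up to 175. The formula and the arithmetic are sound. What is in question is the input rate.

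**Step 2. Identify what 59% is.** 1 − 41/59 = 30.5%, which is the 31% that the section quotes as the lower risk without troponin elevation relative to patients with injury. Both figures are therefore morbidity rates within troponin groups: P(morbidity | elevation) = 59% and P(morbidity | no elevation) = 41%.

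**Step 3. Derive the rate that the analysis will see.** For the joint event in all randomised participants:

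placebo rate = P(injury) × P(morbidity | injury) = P(injury) × 0.59

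This equals 59% only when P(injury) = 100%. Even if every injured patient had morbidity, a joint rate of 59% would need injury in at least 59% of patients.

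**Step 4. Recompute the power.** Held fixed: the protocol's 25% relative reduction, 59% morbidity given injury, and 173 per arm. Power = Φ{[(p₁−p₂)√n − 1.960 √(2p̄(1−p̄))] / √(p₁(1−p₁) + p₂(1−p₂))}.

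Worked case, 40% injury: p₁ = 0.40 × 0.59 = 0.236, p₂ = 0.75 × 0.236 = 0.177, p̄ = 0.2065. Power = Φ[(0.776 − 1.122)/0.571] = Φ(−0.606) = 27%.

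| Injury incidence | Basis | Placebo rate | Rate after 25% reduction | Power at 173/arm | Relative reduction detectable with 80% power |
|---|---|---|---|---|---|
| 22.9% | Discussion, 992/(992 + 3343), 12 h window | 13.5% | 10.1% | 16% | 64% |
| 40% | Introduction, highest-risk patients | 23.6% | 17.7% | 27% | 49% |
| 50% | Assumed | 29.5% | 22.1% | 35% | 43% |
| 60% | Assumed | 35.4% | 26.6% | 43% | 38% |
| 80% | Assumed | 47.2% | 35.4% | 61% | 31% |
| 100% | Limiting case | 59.0% | 44.25% | 79% | 25% |

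The last row gives 79% because exactly 25% off 59% is 44.25%; the article rounds this to 44%.

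**The case against.** **The injury rates come from other settings.** The 40% is a background figure for the highest-risk patients. The 22.9% is a 12 h figure from an earlier cohort, whereas the 59% refers to 24 h and the endpoint counts troponin over days 1 to 3. Incidence in this trial may well be higher. This stands. A reader might infer that 59% is impossible, or that the true power is 16 to 27%. The article supports neither statement, because it gives no incidence for this population and window. It supports only that 59% is not justified as a joint rate and conflicts with the figure in the introduction.

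**Keeping the 25% reduction is a choice.** This also stands. If injury and morbidity given injury each fell by 25%, the joint rate at 40% injury would go from 23.6% to 0.236 × 0.75 × 0.75 = 13.3%, with power of about 70%. The 25% is, however, the effect that the protocol states.

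**The word composite could mean injury or morbidity.** On the article's figures that rate would be 0.229 + 0.771 × 0.41 = 54.5% to 0.40 + 0.60 × 0.41 = 64.6%, a range that includes 59%, with power of about 72 to 86% for a 25% reduction. The endpoint wording and the Discussion both describe morbidity associated with injury, and the Sample size section does not derive 59% as a union. This reading does not stand.

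**Two further criticisms are tempting but fail.** One is that 44% lies close to the 41% seen without injury, so that it removes 15 of the 18 points of excess (83%) and 25% is not conservative. That argument does not fit a joint endpoint, whose rate with no injury is 0%, not 41%. The other is that analysing only injured patients would condition on a post-randomisation event. The article proposes no such analysis.

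**Conclusion.** The concern holds as a wrong input to a correctly executed formula. The 59% is conditional on troponin elevation, while the endpoint is joint and is analysed in all randomised participants.

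Given 59% morbidity among injured patients and a 25% relative reduction, power is below the stated 80% at every injury incidence in the table. The size of the shortfall depends on an incidence that the article does not supply. At its own introductory figure of 40%, power is about 27%; at an assumed 80% it would still be only about 61%. No single power figure should be put in place of 80% without stating the injury incidence behind it.

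**What to change.** 1. In the Primary endpoint section, state that the endpoint is the joint event: myocardial injury and POMS-defined morbidity, both required, counted in all randomised participants.
2. In the Sample size section, replace 59% by a joint placebo rate. Show it as assumed injury incidence times morbidity given injury, and give the basis for the incidence in this population over days 1 to 3.
3. Restate what 350 patients deliver over a range of injury incidence, either as power for a 25% reduction or as the reduction detectable with 80% power (for example about 49% at 40% injury and 38% at 60%).

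The same figures should be carried into the statistical analysis plan. No extra patients, visits or data are needed. The cost is a change of wording and a less favourable stated power.

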### Statistical analysis

A full statistical analysis plan will be developed before any interim or final analysis and published online at https://www.qmul.ac.uk/ccpmg/sops--saps/statistical-analysis-plans-saps/. During the recruitment period, the trial statistician will perform a safety analysis if specifically requested by the DMEC, as outlined in the DMEC charter.

All analyses will be conducted according to the intention-to-treat principle, with all randomised participants with a recorded outcome analysed according to the treatment to which they were randomised. The primary outcome will be analysed using a logistic regression model. The model will be adjusted for minimisation variables (trial centre and planned surgical procedure [surgery involving the gut, all other surgery]). The model will also be adjusted for pre-specified baseline covariates entered into the model as fixed factors. Preoperative heart rate before the first IMP administration will be included as a continuous variable, assuming a linear association with the outcome. The magnitude of the treatment effect will be reported as an adjusted odds ratio (OR) with a 95% confidence interval (CI). Significance will be set at *P*<0.05. Similar analyses of secondary outcomes will be undertaken by intention-to-treat principle, according to the treatment to which they were randomised.

### Pre-specified subgroup analyses

A subgroup analysis will be performed for the primary outcome to assess whether the impact of targeted heart rate control differs in patients at the highest risk of myocardial injury: (1) preoperative heart rate ≥83 beats min^−1^,^12^^,^^13^ (2) raised preoperative NT-proBNP (>100 pg ml^−1^) which is prognostic for poorer perioperative outcomes,^33^^,^^34^ and (3) impaired orthostatic heart rate, an additional measure of cardiac vagal dysfunction.^29^ An additional mechanistic study in a subgroup of patients will explore autonomic changes after ivabradine or placebo dosing through the perioperative period.

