## Abstract

**Background:**

Myocardial injury is strongly associated with excess morbidity and mortality after noncardiac surgery. Higher heart rate may result in perioperative myocardial injury through demand–supply mismatch. Alternatively, higher heart rates may reflect autonomic dysfunction that promotes myocardial injury independently of heart rate. The specific hyperpolarisation-activated, cyclic nucleotide-gated (HCN)-4 (funny) channel inhibitor ivabradine slows the heart rate without altering autonomic control, blood pressure, or myocardial contractility. We hypothesise that individuals with autonomic dysfunction may benefit most from ivabradine reducing heart rate control to minimise myocardial injury-associated morbidity.

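### Effect modification is pre-specified only through high/low groups of continuously measured modifiers; a continuous treatment-by-modifier interaction should be the formal test

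*Protocol article*

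**What the plan says.** Under Pre-specified subgroup analyses, the protocol article plans an analysis of the primary outcome "to assess whether the impact of targeted heart rate control differs in patients at the highest risk of myocardial injury". It lists three groups: preoperative heart rate ≥83 beats/min, NT-proBNP >100 pg/ml, and impaired orthostatic heart rate. The first two have numerical cut-offs; the third has none.

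The hypothesis behind these groups is prominent. The abstract says: "We hypothesise that individuals with autonomic dysfunction may benefit most from ivabradine". The text around Figure 1 repeats it. The last paragraph of the introduction expects a stronger effect with high NT-proBNP, higher resting heart rate or impaired orthostatic response.

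Under Statistical analysis the same heart-rate measurement is kept on its natural scale: "Preoperative heart rate before the first IMP administration will be included as a continuous variable, assuming a linear association with the outcome". There it is an adjustment covariate; no interaction with treatment is mentioned. A full SAP is promised but is not at hand.

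The sample size concerns the overall effect only: "The total sample size is 350 patients, with 175 participants assigned randomly to each arm".

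**The concern.** Resting heart rate, NT-proBNP and the sit-to-stand heart-rate change are all continuous. A single cut-off treats everyone on the same side of it as alike and discards any gradient within each side. The trial is sized for its main effect, so a test of whether that effect varies has little information to spare.

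The heart-rate cut-off also sits awkwardly with the trial's own design. In Table 2 the tablet count changes at 70, at 85 and above 100, not at 83. Patients at 82 and 84 beats/min have the same first dose but fall in different subgroups. The low group mixes patients below 70, whose first dose is omitted, with patients at 70–82, who receive one tablet.

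What is at stake is the mechanistic answer. A null result from an inefficient split could be read as evidence against the autonomic-dysfunction hypothesis when the data could have said more.

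**Working it through.** **The plan's own figure.** Inputs from Sample size: "if ivabradine reduces the incidence of myocardial injury-associated morbidity from 59% (placebo) to 44" percent, and "α=0.05; 1–β=0.8". Sidedness is not stated; two-sided is assumed because it reproduces the figure. With p̄ = (0.59 + 0.44)/2 = 0.515:

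n = [1.960·√(2·0.515·0.485) + 0.842·√(0.59·0.41 + 0.44·0.56)]² / 0.15² ≈ 173.1 per arm.

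This agrees with "173 patients will be required in each arm"; rounding up gives 174. Power at 173 per arm is 0.80. Allowing for 1% dropout, 173/0.99 = 174.7, so 175 per arm. The sample size holds, but it buys 80% power for the overall effect and nothing specific for an interaction.

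**Information kept by a split.** For a normal modifier and a linear interaction, with a share q above the cut-off c, the efficiency of the split relative to the continuous term is

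e = φ(c)² / [q(1 − q)].

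For example, q = 0.20 gives c = 0.842, φ(c) = 0.280 and e = 0.0784/0.16 = 0.49. The last column is the power of the split test when the continuous test has 80%: Φ(2.80·√e − 1.96).

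| q | e | information lost | equivalent n of 350 | power of split |
|---|---|---|---|---|
| 10% | 0.342 | 66% | 120 | 37% |
| 20% | 0.490 | 51% | 171 | 50% |
| 30% | 0.576 | 42% | 201 | 57% |
| 50% | 0.637 | 36% | 223 | 61% |

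The loss is smallest at q = 50% and symmetric around it, so 36% is the minimum under these assumptions.

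**Simulation check.** The settings were a logistic model with n = 346 (2 × 173), a standard normal modifier, 59% placebo risk and a treatment log odds ratio of −0.605 at the modifier's mean, a prognostic slope of 0.2 and an interaction of −0.65 per SD, with about 1,500 runs for each q. Power, continuous versus split:

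- q = 10%: 0.83 vs 0.34
- q = 20%: 0.83 vs 0.52
- q = 30%: 0.81 vs 0.58
- q = 50%: 0.83 vs 0.65

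**Which q applies?** The article gives no distribution for any modifier.

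- *Heart rate:* assumed means of 70–78 and SDs of 10–14 beats/min put 10–36% at or above 83, a loss of 66–39%. That is about 17–63 patients per arm (175 × 0.097 to 175 × 0.36).
- *NT-proBNP:* q cannot be derived. If about half exceed 100 pg/ml the loss is 36%. Normality would more plausibly hold on the log scale.
- *Orthostatic response:* no cut-off is stated, so no loss can be computed.

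**What if the effect follows the dose steps?** Take the same heart-rate distributions and let the treatment effect be proportional to the first-dose tablet count in Table 2 (0, 1, 2, 3). The squared correlation with that pattern is 0.74–0.86 for a linear heart-rate term and 0.36–0.65 for the ≥83 split. The split is then 49–76% as efficient as the linear term.

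**The case against.** The strongest reply has four parts.

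1. *The SAP may add a continuous analysis.* The article condenses a fuller plan and does not say which test the subgroup analysis uses. A reader might infer that a split is the only test the trial will ever run; the article does not show that. What stands is narrower: for these modifiers it does state a form of analysis, under a heading that calls it pre-specified, and every form it names is a category.

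2. *The hypothesis may concern groups, not gradients.* The wording about dysfunction, high NT-proBNP and impaired response can be read that way; only higher resting heart rate reads plainly as a gradient. If the effect truly steps at the cut-off, the split is efficient and a linear term pays the same 36–66% penalty. This is correct in general, so the split cannot be called the least informative analysis available. It does not rescue 83 beats/min: that value is cited for its association with myocardial injury, and Table 2 has no step there.

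3. *A linear term can also be wrong.* Dosing is stepped, and the Discussion allows that lowering heart rate might harm if heart rate is only a marker. This stands, and is why the fix includes a non-linearity check.

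4. *Importance.* The primary comparison is untouched, the two numerical cut-offs are referenced rather than data-driven, and a separate mechanistic study is planned. All true; they limit the weight of the point without removing it.

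Nor does continuous heart rate in the primary model contradict the subgroup plan. Adjusting for a continuous covariate while displaying categories is ordinary practice; it only shows that the continuous form is already at hand.

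**Conclusion.** The point holds in a conditional form. The article names its effect-modification analyses only as high/low groups of continuously measured variables. With a normal modifier and an approximately linear interaction, that costs at least about 36% of the information, and about 42–66% if 10–30% of patients exceed the cut-off.

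A reader might infer that a loss of this larger size applies to all three modifiers because few patients exceed the cut-offs. The documents do not support that. The share is an assumption: plausible for heart rate, unknown for NT-proBNP, and not calculable for orthostatic response.

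A reader might also infer that a patient at 82 beats/min is treated and one at 60 is not. Under Table 2 that is true of a single administration only, because heart rate is reassessed before each of the six.

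This is a worthwhile improvement to an important secondary question, not a flaw in the primary analysis.

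**What to change.** Before unblinding, specify in the SAP:

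- The formal effect-modification test is the treatment-by-continuous-modifier interaction in the primary logistic model, one modifier per model: heart rate in beats/min, log NT-proBNP, and sit-to-stand heart-rate change. Include the modifier's main effect in each.
- One simple pre-specified check for non-linearity, for example a restricted cubic spline for the modifier and its interaction.
- A plot of the estimated treatment effect, with its confidence band, across the observed range of each modifier.
- The cut-off groups remain as descriptive rows in a forest plot, with the orthostatic threshold stated.

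The cost is SAP wording and a few lines of code. No new data, visits or patients are needed. The downside is that a linear term is less efficient if the effect truly steps at the cut-off, and there is slightly more analysis work.
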